### Study procedure

Patients participating in the study will be recruited from our PED. Every patient presenting to PED will be triaged by the admitting nurse. During the study period, any admission meeting the inclusion and exclusion criteria will be eligible for enrolment in our protocol during the day, depending on the availability of the clinical study technician. On arrival, an initial clinical assessment will be performed. A clinical study technician will then explain the objective and procedures of the study to the parents and to the child if they are of sufficient age and maturity to understand. After obtaining informed consent and registering the child, participants will be seated with their parents in a quiet office, where lighting conditions will be optimised to ensure accurate functioning of the Caducy application. The following data will then be collected: sex, age and phototype according to Fitzpatrick’s classification ranging from phototype 1 to 6.^9^ The child will be seated on a chair facing a camera connected to a laptop running the Caducy Medical Device software. Simultaneously and according to standard clinical procedure, three thoracic ECG electrodes will be placed on the patient, used to measure both HR and RR. The first two electrodes will be positioned on the mid-clavicular lines at the level of the second intercostal spaces, while the third electrode will be placed subcostally on the left side. The electrodes will then be connected to a Mindray ePM10 monitor. Once the child is calm and correctly positioned, the Caducy application will be initiated. Simultaneously, the Mindray monitor will record vital signs. To facilitate patient cooperation, hypnotic visual stimuli—such as kaleidoscope-type videos—will be displayed during image capture; these videos will have a dark tone to specifically reduce interference from ambient lighting. After 30 and 60 s, the HR and RR values obtained from the Caducy application (using the rPPG method) will be collected. Concurrently, HR and RR values from the Mindray monitor will also be recorded for comparison and clinical purposes (figure 1). The total duration of each patient’s participation is estimated at approximately 20 min, including preparation and data collection.

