### Primary endpoint

Analysis of reliability between HR measured by the gold standard (ECG via Mindray ePM10) and HR measured by rPPG (using the Caducy application) following a 30-s recording period. Up to two measurement attempts will be permitted for each method. If a successful measurement is not achieved within two attempts for either method, the primary endpoint will be considered unevaluable for that participant.

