### Secondary endpoints

Reliability between gold standard (ECG) HR measurements and rPPG HR measurements using a recording period of 60 s.Reliability between gold standard (impedance RR measure via Mindray ePM10) RR measurements and rPPG RR measurements using a recording period of 60 s.Reliability between gold standard RR measurements and rPPG RR measurements using a recording period of 30 s.Reliability of HR measurements between the Mindray ePM10 and rPPG over 30 s, stratified by age group (3 years to 7 years, 7 years to 12 years and 12 years to 18 years) and by Fitzpatrick skin phototype classification.Reliability of RR measurements between the Mindray ePM10 and rPPG over 30 s, stratified by age group (3 years to 7 years, 7 years to 12 years and 12 years to 18 years) and by Fitzpatrick skin phototype classification.Parental satisfaction with the use of the Caducy application, assessed using a 5-point Likert scale (1=‘Not at all useful’ to 5=‘Extremely useful’).Participant satisfaction (children/adolescents aged 3–17 years) with the use of the Caducy application, assessed using a 5-point Likert scale (1=‘Not at all useful’ to 5=‘Extremely useful’).Rate of measurement failure for each technique (rPPG and thoracic electrodes), defined as the inability to obtain a valid measurement value or the presence of clearly erroneous measurements attributable to poor signal quality or acquisition failure.

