### Statistical analysis

Analyses will be performed by a biostatistician from the Department of Clinical Research at the CHU of Nice. The assumptions underlying each statistical test will be verified prior to analysis. Results will be considered statistically significant at the 5% level (p<0.05), unless specified otherwise. Analyses will be conducted using SAS Enterprise Guide V.7.1 (SAS Institute Inc., Cary, NC, USA). Descriptive statistics will be calculated for the study population and key study parameters. Categorical variables will be presented as absolute and relative frequencies, with 95% CIs where appropriate. Quantitative variables will be presented using means, SD, medians and IQRs. A flowchart illustrating participant flow (including numbers included and followed up) will be provided. Reliability will be assessed using the intraclass correlation coefficient (ICC) with a 95% CI to measure the agreement between the two measurement systems. Missing data will not be imputed.

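### Returned readings judged clearly erroneous count as failures; if failures are not successful measurements, gross rPPG errors can leave the primary ICC by a call not required to be blind to the ECG

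*Protocol article*

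**What the plan says.** Four statements in the protocol article bear on this point.

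- **Primary endpoint.** Heart rate from the ECG is compared with heart rate from rPPG over a 30-s recording, and either device may be tried twice. The consequence of failing is explicit: "If a successful measurement is not achieved within two attempts for either method, the primary endpoint will be considered unevaluable for that participant". The section does not say what makes a measurement successful.
- **Secondary endpoints.** The last item is the failure rate of each of the two techniques. A failure there means "the inability to obtain a valid measurement value or the presence of clearly erroneous measurements attributable to poor signal quality or acquisition failure". This is the only definition of a failed measurement in the article. Its second limb covers values that the device did return.
- **Study procedure.** The two devices run at the same time: "Concurrently, HR and RR values from the Mindray monitor will also be recorded for comparison and clinical purposes". The article does not say who decides that a reading is erroneous, or whether that person can see the other device's value.
- **Statistical analysis.** Agreement is summarised by an ICC and its 95% CI. On gaps in the data the section is brief: "Missing data will not be imputed". A child who is unevaluable therefore does not contribute to the ICC.

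**The concern.** An agreement study measures how far the new device departs from the reference. If large departures can be set aside as failed readings before the ICC is computed, the ICC describes only the readings that were accepted.

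Three features make this a practical risk. The criterion is a judgement with no numerical or signal-quality threshold. It concerns erroneous values, and the most visible sign of an error is the ECG value recorded at the same moment. A rejected first attempt can be replaced by a second, so a disagreement can disappear while the child stays in the analysis and the number evaluable hardly changes.

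The study aim covers both feasibility and accuracy, and the Discussion foresees use by parents and in teleconsultation, where there may be no ECG against which to reject a reading. An ICC limited to accepted readings would overstate the agreement such users could expect from the values on their screen.

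**Working it through.** **1. How the rules combine.** A returned but clearly erroneous value, attributed to poor signal or acquisition failure, is a failure (Secondary endpoints). If a failure is not a success, the first such reading leads to a second attempt, and a second one makes the child unevaluable (Primary endpoint). The child then leaves the ICC, because nothing is imputed (Statistical analysis). The second step is an inference: the two sections do not refer to each other. If it is wrong, successful has no definition at all for the primary endpoint.

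**2. The plan's own yardstick.** Sample size assumes an ICC of 0.90 with precision ±0.02, type I error 5% and type II error 10%, and states 430 participants. Reading the type II error as 90% assurance of that precision, with SE = (1 − ρ²)/√(n − 1):

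- at n = 429, SE = 0.19/√428 = 0.00918;
- lower value of ρ = 0.90 − 1.2816 × 0.00918 = 0.8882;
- half-width = 1.96 × (1 − 0.8882²)/√428 = 0.0200.

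This gives 429, which reproduces the stated 430. With the 10% technical allowance, 430/0.90 = 478 are needed, and 600 × 0.90 = 540 would remain. Numbers are therefore not the problem. The yardstick for a bias is ±0.02.

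**3. Size of the effect.** The documents give no variances or error rates, so these are assumptions: true heart-rate SD 20 bpm, ECG error SD 3, ordinary rPPG error SD 5, a fraction f of rPPG readings with an added gross error of SD 30, and rejection of pairs more than 20 bpm apart. Over all returned values,

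ICC = 400 / [400 + (9 + 25 + 900f)/2].

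For f = 5% this is 400/(400 + 39.5) = 0.910. The ICC after rejection comes from simulation.

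| Gross errors | ICC, all returned values | ICC, after rejection | Rise |
|---|---|---|---|
| 1% | 0.949 | 0.959 | 0.010 |
| 2% | 0.939 | 0.959 | 0.020 |
| 3% | 0.929 | 0.958 | 0.029 |
| 5% | 0.910 | 0.957 | 0.047 |
| 10% | 0.866 | 0.954 | 0.088 |

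The rise is below the planned precision at 1%, about equal to it at 2%, and 1.5 to more than 4 times as large from 3% to 10%. If only half of the pairs beyond 20 bpm were rejected at f = 5%, the ICC would go from 0.910 to 0.933.

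**4. Effect of the second attempt.** At f = 5%, about 2.6% of first attempts are rejected. If the second attempt is independent, 0.026² = 0.07% of children fail twice, which is 600 × 0.0007 = 0.4 of a child. The ICC still rises from 0.910 to 0.957. The count of unevaluable children would therefore give almost no sign of the effect. Independence is an assumption; a restless child may well fail twice, and more children would then become unevaluable.

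**5. Other error models.** Suppose instead that the ICC among accepted readings is 0.90, and add back gross errors that are unrelated to the true rate, uniform on 50–180 bpm, or a 40 bpm undercount. The ICC over all returned values is then about 0.88–0.89 at 1%, 0.86–0.88 at 2%, 0.80–0.86 at 5% and 0.72–0.81 at 10%. The direction is the same, and the size is similar or larger.

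**The case against.** - **The link is not stated.** The clearly erroneous wording belongs to a secondary endpoint, and the primary rule does not cite it. This stands, and it is why the conclusion is conditional.
- **Disagreement alone is not a failure.** The wording requires the error to be attributable to poor signal quality or acquisition failure, so a discordant value with a sound signal stays in the ICC. A reader might infer that the protocol removes readings for differing from the ECG, or that unblinded staff make the call. The article says neither; it is silent on who decides and what they can see. What remains is that no objective criterion ties the judgement to the signal.
- **Failures are reported.** A reader might infer that they are hidden. They are not: the failure rate of each technique is an endpoint, and a participant flowchart is planned. The rule also applies to both devices. Agreement among valid readings plus a failure rate is a recognised pair of summaries, defensible if validity is fixed objectively and without sight of the other device. But the rate shows how often readings failed, not how wrong they were. The article does not say whether it is counted per attempt or per child.
- **The 20 bpm cut-off and error rates are assumptions.** True. Without gross errors the assumed device has an ICC of 400/(400 + 17) = 0.959, so the values after rejection essentially recover its performance with a sound signal. The rise is a bias only if the ICC is read as covering every value the device returns.
- **The full protocol may define validity.** It may. But this article states both the failure definition and the exclusion rule, and a rejected reading that was never recorded cannot be restored at analysis.

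**Conclusion.** The concern holds in conditional form. If a measurement failure is not a successful measurement, gross rPPG errors attributed to poor signal or acquisition failure are replaced or dropped from the primary ICC by a subjective call that nothing requires to be made blind to the ECG. The ICC then describes accepted readings and can be biased upward.

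Under the assumed inputs, the rise runs from about 0.01 at 1% gross errors to about 0.09 at 10%, and it reaches the planned ±0.02 at about 2%. The true size depends on the gross-error rate and on how readings are rejected in practice, neither of which the document gives. Enrolling 600 children does not reduce it.

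A reader might go further and conclude that the primary ICC is certainly inflated, or that the design selects on the size of the disagreement. The text does not support that: it sets no comparison with the ECG and no cut-off, and it limits failures to signal or acquisition problems.

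**What to change.** 1. Define a successful rPPG reading from the device's own output or signal quality alone, decided without sight of the ECG value. Judge ECG validity without sight of the rPPG value. State that this definition governs both the primary endpoint and the failure rate.
2. Record every returned value from every attempt, including rejected ones, with the reason for rejection. This has to be in place while readings are being collected.
3. Keep the two-attempt primary ICC. Report beside it a pre-specified ICC that uses the first returned rPPG value of every child with a valid ECG, and count failures per attempt as well as per child.

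Making the first returned value the primary analysis would be a larger change. It would override the two-attempt design and alter what the primary ICC estimates, so it is a trade-off and not needed to meet this point.

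The cost is revised wording, additional fields in the case report form and one extra table, with no extra participants or procedures. The companion ICC may be less favourable than the primary one.

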### Statistical analysis

Analyses will be performed by a biostatistician from the Department of Clinical Research at the CHU of Nice. The assumptions underlying each statistical test will be verified prior to analysis. Results will be considered statistically significant at the 5% level (p<0.05), unless specified otherwise. Analyses will be conducted using SAS Enterprise Guide V.7.1 (SAS Institute Inc., Cary, NC, USA). Descriptive statistics will be calculated for the study population and key study parameters. Categorical variables will be presented as absolute and relative frequencies, with 95% CIs where appropriate. Quantitative variables will be presented using means, SD, medians and IQRs. A flowchart illustrating participant flow (including numbers included and followed up) will be provided. Reliability will be assessed using the intraclass correlation coefficient (ICC) with a 95% CI to measure the agreement between the two measurement systems. Missing data will not be imputed.

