**Methods and analysis:**

This is a monocentric, prospective study enrolling 600 paediatric participants. Each participant will have standard monitoring electrodes (ECG/impedance) placed on the chest while seated facing a camera for rPPG recording. Simultaneous HR and RR measurements will be recorded over periods of 30 and 60 s using both the standard monitor and the rPPG device. The intraclass correlation coefficient will be calculated to assess agreement between the rPPG and standard monitor measurements.

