#### Eligibility criteria

Eligibility and exclusion criteria are listed in table 1.

**Table 1 T1:** List of eligibility and exclusion criteria

Eligibility criteria	Exclusion criteria
Age 3 to 17 years Admitted to the PED Signed consent by one of the two parents or the holder of parental authority Affiliation to a national social security scheme	Presence of vital distress Absence or withdrawal of parental consent Patients with neurocognitive conditions Medical history of cardiac arrhythmia, pathological tremors, muscle spasms, scleroderma Patients whose parents or legal guardians do not understand and/or speak French

PED, paediatric emergency department.

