### Sample size

We hypothesise an ICC of 0.90. To estimate this ICC with a precision of ±2% and considering a type I error of 5% and a type II error of 10%, the required sample size is 430 participants.^12^ To account for potential technical issues (10%), to facilitate subgroup analyses and considering our active patient pool, the total targeted sample size in this study will be 600 participants.

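### The ICC is the only agreement measure named, with its form unstated; an ICC of 0.90 fixes no error in beats per minute, and no between-device bias estimate is planned

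*Protocol article*

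**What the plan says.** The Study aim section sets out to evaluate feasibility and accuracy in children. The Primary endpoint section asks for reliability between ECG heart rate and rPPG heart rate over 30 s. The Abstract says "The intraclass correlation coefficient will be calculated to assess agreement between the rPPG and standard monitor measurements", and the Statistical analysis section says "Reliability will be assessed using the intraclass correlation coefficient (ICC) with a 95% CI to measure the agreement between the two measurement systems". Neither place says whether the ICC measures consistency or absolute agreement.

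Table 1 admits children of "Age 3 to 17 years", and the primary endpoint is not split by age. The Secondary endpoints section does plan heart rate and respiratory rate reliability at 30 s by three age groups and by Fitzpatrick phototype.

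The Sample size section states "We hypothesise an ICC of 0.90" and derives 430 participants from a precision of ±2%, raised to a target of 600. Nowhere does the article name a mean difference between devices, limits of agreement, or an acceptable error in beats or breaths per minute.

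**The concern.** The clinical question is whether a camera reading can stand in for a monitor reading in an individual child. The answer lies in the size of the paired difference, in beats or breaths per minute, and in whether it leans one way.

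The ICC is between-child variance divided by total variance. For a given device error it rises as the children differ more from one another, and pooling ages 3 to 17 tends to widen that spread. It does not show the direction of a bias or whether error grows at fast rates.

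The Discussion says that results in line with the hypothesis could support use of the device, and it looks ahead to use by parents, in teleconsultation and by emergency services. With only an ICC and its interval, a reader could not tell what error in an individual child lies behind that conclusion.

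This is more than a detail left to an analysis plan: the article names the agreement measure and sizes the trial on it.

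**Working it through.** **Inputs from the Sample size section.** ICC 0.90, half-width 0.02, type I error 5%, type II error 10%, two devices. **Assumed.** Between-child SD (SDb), because the article gives none: 15, 20 and 25 bpm for heart rate, and 4 to 8 breaths/min for respiratory rate.

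**1. The plan's own figure.** For a one-way ICC with two readings, the standard error is (1 − r²)/√(N − 1), which is 0.19/√(N − 1) at r = 0.90.
- The expected 95% half-width is 1.96 × 0.19/√(N − 1). Setting it to 0.02 gives N = 348.
- For 90% assurance, add 1.2816 times the SD of the half-width, which is 1.96 × 2r × 0.19/(N − 1) = 0.670/(N − 1).
- At N = 430: 0.01798 + 1.2816 × 0.001562 = 0.01998, within 0.02. At N = 429 the sum is 0.02001, just over.

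So "the required sample size is 430 participants" reproduces exactly, as precision with 90% assurance. A 10% allowance gives 430/0.9 = 478, below the 600 planned. The sample size is not in question.

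**2. What 0.90 means in bpm, with no bias.** Error variance per device = SDb² × (0.1/0.9). SD of the paired difference = √(2 × error variance). Limits of agreement = ±1.96 × that SD.

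| SDb (bpm) | Error variance | SD of difference | 95% limits (bpm) |
|---|---|---|---|
| 15 | 25.0 | 7.07 | ±13.9 |
| 20 | 44.4 | 9.43 | ±18.5 |
| 25 | 69.4 | 11.79 | ±23.1 |

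For respiratory rate the same formula gives ±3.7 breaths/min at SDb 4 and ±7.4 at SDb 8. If the assumed SD is instead the total SD of one device's readings, the heart rate limits are 0.877 × SD: ±13.1, ±17.5 and ±21.9 bpm.

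**3. Effect of spread.** Hold the error variance at 44.4 (pooled ICC 0.90 at SDb 20). In an age band with SDb 15 the ICC is 225/(225 + 44.4) = 0.84; with SDb 12 it is 144/(144 + 44.4) = 0.76. The device error in bpm is the same in all three.

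**4. Effect of bias.** For two devices, a constant offset b adds b²/2 to the denominator of an absolute-agreement ICC and nothing to that of a consistency ICC.
- At SDb 20, an agreement ICC of 0.90 leaves 400/0.9 − 400 = 44.4 for offset and scatter together.
- With b = 3, scatter is 44.4 − 4.5 = 39.9 and the consistency ICC is 400/439.9 = 0.91.
- With b = 5, scatter is 44.4 − 12.5 = 31.9 and the consistency ICC is 400/431.9 = 0.93.
- With scatter kept at 44.4 and b = 10, consistency stays at 0.90 while agreement falls to 400/(444.4 + 50) = 0.81.
- With no scatter, an agreement ICC of 0.90 allows b = √(2 × 44.4) = 9.4 bpm.

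The absolute-agreement form therefore penalises bias but cannot separate it from scatter.

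**5. Precision at the planned size.** Take SDb 20, no bias, and n = 430 or 540 (600 less 10%).
- Mean difference: 1.96 × 9.43/√n = ±0.9 or ±0.8 bpm.
- Each limit: 1.96 × 9.43 × √(1/n + 1.96²/(2(n − 1))) = ±1.5 or ±1.4 bpm.

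**The case against.** Several points on the other side stand.

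- The age-stratified analyses act directly on the pooling problem: step 3 shows that a fall in ICC within bands would be visible. They are secondary, however, cover only 30 s, and name no measure in native units.
- No heart rate SD is given, and the setting may narrow the spread. Children in vital distress or with a history of arrhythmia are excluded, and measurement is made seated in a quiet room once the child is calm.
- A reader might infer that systematic bias will go unreported. The article does not support that. Means are promised for key study parameters and may include each device's readings, whose difference over the same children is the bias. An absolute-agreement ICC would also penalise an offset. The 430 comes from a one-way formula, which counts bias as error; that suggests, but does not prove, that such a form is intended. What holds is that no bias estimate is planned in the text. Separate device means also give no SD of the paired difference, so limits of agreement cannot be recovered from them.
- A reader might infer that 0.90 is a success threshold that a poor device could pass. It is the planning value of a precision calculation. The Discussion ties support for the device to the hypothesis, but also calls for more paediatric validation before wide use.
- A fuller analysis plan, not shown, may add limits of agreement. Nothing in the article commits to them, and the measure it does name falls short of the stated aim of accuracy.

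**Conclusion.** The concern holds in a limited form. The ICC is the only agreement measure named, its form is open, and it cannot by itself answer a question about accuracy. At 0.90 with no bias, limits of agreement run from ±13.9 to ±23.1 bpm over assumed between-child SDs of 15 to 25 bpm. That range illustrates how little 0.90 fixes; it does not predict how this device will perform. If a consistency form were used, agreement of 0.90 with an offset of 3 or 5 bpm would read as 0.91 or 0.93 (SDb 20).

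The documents do not support a claim that errors of about ±18 bpm will occur, or that bias will necessarily stay hidden. The remedy needs only the paired readings already to be recorded, so nothing is lost if it is settled before database lock.

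**What to change.** Keep the ICC as the primary statistic and state its form: absolute agreement, single measurement.

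Beside it, for heart rate at 30 s, report the mean rPPG-minus-ECG difference and the 95% limits of agreement, each with confidence intervals in bpm, and a difference-versus-mean plot. Give these overall and by the planned age bands and phototypes. Report the same for the respiratory rate and 60 s comparisons as secondary results, in their own units; they need not become co-primary.

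The sponsor should state, before database lock, the acceptable difference it will use for interpretation.

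The cost is a few sentences, tables and plots from data already to be collected, and possibly a less favourable ICC than a consistency form would give. No extra patients are needed.
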